## Objective

The objective of the RISAP study is 1) to systematically develop, describe and evaluate a complex intervention comprising a training programme for GPs in risk communication and shared decision-making, 2) to evaluate the effect of the training programme on real-life consultations between GPs and patients with high cholesterol, and 3) to evaluate the patients' reactions during and after the consultations and adherence to chosen treatment plans.

RISAP is an acronym for **Ris**k Communication in Gener**a**l **P**ractice.

The hypotheses are that the intervention group patients will have higher adherence to chosen treatment, have better self-rated health and fewer contacts with health services, have better satisfaction with treatment decision, and experience no increased anxiety, compared to the control group patients.

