### Outcomes

The primary patient outcome is adherence to treatment choice. Secondary patient outcomes are self-rated health, anxiety, satisfaction with decision, enablement, satisfaction with communication, satisfaction and confidence in decision, and number of contacts to health services.

The primary GP outcome is satisfaction with decision.

Secondary GP outcomes are GP attitudes towards risk communication and towards preventive treatment of cardiovascular disease, patient involvement in decision-making, and use of risk communication tools.

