### Outcome measurement

The patients will receive a questionnaire at baseline and after 3 and 6 months. It includes questions from validated scales: the Morisky Compliance Scale is used to assess adherence to chosen treatment, defined as 80% of the scheduled treatment taken as prescribed [52-54]. Self-rated health will be measured with questions from SF-12 [55-64], and patient enablement will be measured with the Patient Enablement Instrument [65]. Risk communication and decision-making effectiveness will be measured using the COMRADE scale [66]. In addition, the questionnaire will include questions on the patients' socio-demographic circumstances.

Prescriptions, contacts to the health services, and cholesterol level will be drawn from the register of the National Health Service of Denmark at baseline and at 6 months. The cholesterol level will be measured only on the GP's own initiative.

The GPs will receive a questionnaire at baseline and after 6 months about attitudes towards risk communication and cholesterol-reducing medication. After each consultation with a participating high cholesterol-patient, the GPs will complete a questionnaire about decision satisfaction with questions from the Provider Decision Process Assessment Instrument [67]. In addition, the GP will be asked to identify which, if any, risk communication tools were used during the consultation.

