### Data analysis

Descriptive statistics will be generated for all variables. All analyses will be intention to treat. Data concerning adherence will be analysed by multivariate binomial regression with a latent variable with a level for each practice. Multivariate logistic regressions models will be used to determine variables independently associated with the outcome variable for questionnaire data. Missing responses will be excluded from the analysis. A probability level of p < 0.05 based on two-sided tests is considered statistically significant.

The qualitative research process will be iterative, alternating between data production, analysis, and theory. Informal analysis has been conducted in the developmental stage of the study and continues in a kind of funnel structure of "progressive focusing" [51]. The data from the interviews will be transcribed verbatim, and these transcriptions and written field notes will undergo a thematic analysis in which key patterns will be identified and grouped into themes [68]. The core themes and their meanings and interrelations will be explored and interpreted, using appropriate formal theories [69].

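### The stated aim of the questionnaire models is to find associated variables; it should be to estimate the randomised-arm contrast that the hypotheses and the primary GP outcome call for

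*Protocol article*

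**What the plan says.** All quotations are from the protocol article.

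- **Questionnaire outcomes** (Data analysis): multivariate logistic regression models "will be used to determine variables independently associated with the outcome variable for questionnaire data". This is the only model given for questionnaire data other than adherence.
- **Adherence** (Data analysis): "Data concerning adherence will be analysed by multivariate binomial regression with a latent variable with a level for each practice".
- **Analysis principle** (Data analysis): "All analyses will be intention to treat".
- **Hypotheses** (Objective): these compare the arms. Besides adherence, self-rated health and contacts, intervention patients are expected to "have better satisfaction with treatment decision, and experience no increased anxiety, compared to the control group patients".
- **GP outcome** (Outcomes): "The primary GP outcome is satisfaction with decision". Under Outcome measurement it is collected by questionnaire after each consultation with a participating patient.
- **Tool use** (Outcome measurement): "the GP will be asked to identify which, if any, risk communication tools were used during the consultation". The Outcomes section also lists use of these tools as a secondary GP outcome.

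**The concern.** A model built to find out what is independently associated with satisfaction answers a different question from one built to find out whether the training changes satisfaction. In the first, allocation is one explanatory variable among several. In the second, it is the quantity of interest, and the other terms are there only for precision or to respect the design.

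The difference matters here because the trial records variables that the training is meant to change. Tool use is the clearest case: the workshops teach the tools, and the GP then reports which were used. It is a natural candidate in a search for variables associated with satisfaction. Once it is in the model, the arm coefficient describes only the part of the effect that does not run through the tools. A reader could take a small coefficient as evidence that the training did not work.

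At stake are the primary GP outcome and the patient outcomes measured by SF-12, the Patient Enablement Instrument and COMRADE.

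**Working it through.** **1. Plan figures.** The article gives no power or effect size for questionnaire outcomes other than adherence, so there is no plan figure to reproduce on this point. Its one such figure, 90% power for non-adherence of 20% v 10%, concerns another outcome. For completeness: with a between-GP SD of ln(0.50/0.08)/3.92 = 0.4675 on the log scale, medians of 0.20 and 0.10, and 40 practices of 7 patients per arm, a random-intercept log-link model gave simulated power of 0.88. That is close to the stated figure and does not bear on the concern.

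**2. Question against model.**

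| Outcome | Source | Question | Stated model aim |
|---|---|---|---|
| Adherence | Questionnaire | Arm difference, powered as such under Sample size | Binomial regression with practice-level latent variable; no competing aim |
| GP decision satisfaction (primary GP outcome) | Questionnaire after each consultation | Effect of the training | Find independently associated variables |
| SF-12, enablement, COMRADE | Questionnaire | Intervention v control | Find independently associated variables |
| Contacts with health services | Register | Intervention v control | Not covered by the logistic sentence |

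The mismatch is in rows 2 and 3.

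**3. What the permitted adjustment could do (illustration only).** Every input here is assumed except the 80 practices of 7 patients. Assume tool use in 80% of intervention and 20% of control consultations, log-odds of satisfaction of −0.3 without tools, an increase of 1.0 with tools, no other path from training to outcome, and a practice SD of 0.5 on the logit scale.

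By hand, ignoring practice variation:
- P(satisfied, no tool) = 1/(1 + e^0.3) = 0.426
- P(satisfied, tool) = 1/(1 + e^−0.7) = 0.668
- Intervention: 0.8 × 0.668 + 0.2 × 0.426 = 0.620
- Control: 0.2 × 0.668 + 0.8 × 0.426 = 0.474
- Arm odds ratio = (0.620/0.380)/(0.474/0.526) = 1.81
- Arm odds ratio given tool use = e^0 = 1, by construction

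Simulation with practice variation (400 runs per row, logistic regression, standard errors clustered by practice, two-sided 5%):

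| Tool-use log-odds | Direct log-odds | Arm-only OR | Significant | OR with tool use in model | Significant |
|---|---|---|---|---|---|
| 0.6 | 0 | 1.41 | 44% | 1.00 | 5.5% |
| 1.0 | 0 | 1.74 | 81% | 0.99 | 3.5% |
| 1.4 | 0 | 2.20 | 98% | 1.00 | 4% |
| 1.0 | 0.3 | 2.30 | 98.5% | 1.34 | 24.5% |

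Monte Carlo error is about √(0.81 × 0.19/400) = 0.02 at 81% and √(0.035 × 0.965/400) = 0.01 at 3.5%. With practice variation the 1.81 becomes about 1.74. In the last row, where part of the effect bypasses the tools, the adjusted model recovers only that direct part (e^0.3 = 1.35).

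**The case against.** The strongest reply is that the sentence is loosely worded shorthand. The same paragraph applies intention to treat to all analyses, the hypotheses are framed between arms, and the design is a cluster-randomised trial. A multivariable model that asks whether allocation is independently associated with the outcome would fit all of this. The adherence sentence does not name arm either. A fixed covariate list is normally left to an analysis plan, which is not shown.

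Much of this stands, and it rules out several stronger readings that a reader might infer:

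- *That the arms will not be compared on questionnaire outcomes.* The article does not say so, and arm may well be in the model.
- *That the plan adjusts away the training's effect.* No covariate is named anywhere. Tool use, enablement and GP satisfaction are listed as outcomes. Socio-demographic data are ordinary covariates, and GP attitudes are also measured at baseline.
- *That predictors will be selected at p < 0.05.* The article gives this as the general significance level and describes no selection procedure or number of candidates, so no false-positive rate can be calculated.
- *That all secondary hypotheses are affected.* Contacts are register data.
- *That the primary GP outcome rests on about 80 GPs.* It is recorded per consultation, so the planned minimum is 2 × 40 × 7 = 560 records, clustered by practice.

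The reply does not remove the core point. Intention to treat settles who is analysed and in which group; it neither keeps arm in a regression nor bars covariates measured after randomisation. The adherence sentence states no rival aim, and the Sample size section supplies its arm contrast; no such support exists for the other questionnaire outcomes. Nor is the article silent, leaving the matter to a later plan: it states an aim, and a plan that followed it faithfully would carry the mismatch forward.

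**Conclusion.** The concern holds in a limited form: the analysis aim is badly fixed. The stated purpose of the questionnaire models does not match the between-arm hypotheses, and this affects the primary GP outcome and the SF-12, enablement and COMRADE outcomes. Adherence and register-based contacts are outside it.

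Loss of a real training effect is something the wording permits, not something the article plans. Its size cannot be derived from the document. The fall of the arm odds ratio to about 1 follows from assuming full mediation through tool use; with the assumed direct path it fell from 2.30 to 1.34. These figures show the direction of the hazard and are not estimates for this trial. The finding itself rests on the wording and does not need them.

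**What to change.** Replace the questionnaire sentence in the Data analysis section with a statement that:

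1. for each questionnaire outcome, including GP decision satisfaction, the effect estimated is the contrast between randomised arms;
2. it comes from one fixed model in which arm is always retained;
3. covariates are limited to baseline variables and the randomisation strata (practice type, gender, age, urban or rural), with nothing measured after randomisation (tools used, treatment chosen, other outcome scales);
4. the model carries the practice-level term already planned for adherence;
5. any search for independently associated variables, and any analysis of tool use as a mediator, is reported separately as exploratory and is not used to judge the hypotheses in the Objective section or the primary GP outcome.

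The cost is a change of wording and slightly more analysis work. No data collection or sample size changes, and the predictor analysis is kept under its proper label.

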### Sample size

A simulated power calculation shows that a trial with 40 practices in each group (at least 1 GP per practice and at least 7 patients with high cholesterol per GP) ensures a statistical power of 90% for detecting a 10% difference in lack of adherence (from 20% to 10%) at a significance level of 5%. The patients' adherence rates are assumed to vary from GP to GP according to a normal distribution on a logarithmic scale. The variance of the latent normal distribution is determined by assuming that 95% of the patients adherence levels within each GP vary within the intervals 0.08 to 0.50 (active control group) and 0.04 to 0.25 (experimental group).

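### Excluding missing responses drops non-responders from the self-reported primary outcome, which makes the intention-to-treat promise incomplete and may bias the result if reply depends on adherence

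*Protocol article*

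**What the plan says.** The Outcomes section states: "The primary patient outcome is adherence to treatment choice". Outcome measurement says how: "the Morisky Compliance Scale is used to assess adherence to chosen treatment, defined as 80% of the scheduled treatment taken as prescribed". The instrument reaches patients by questionnaire: "The patients will receive a questionnaire at baseline and after 3 and 6 months". A second source does not depend on a reply: "Prescriptions, contacts to the health services, and cholesterol level will be drawn from the register", at baseline and at 6 months.

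Data analysis states "All analyses will be intention to treat". It assigns adherence to a binomial regression with a latent variable for practice and other questionnaire data to logistic regression. The next sentence is the missing-data rule: "Missing responses will be excluded from the analysis".

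Sample size plans for non-adherence of 20% v 10%, 40 practices per arm and at least 7 patients per GP, with 90% power. The article states no expected response rate and no assumption about why replies would be missing.

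**The concern.** The exclusion rule is a decision written into the protocol, not a detail left open. Applied to a self-reported primary outcome, it makes the analysed set the patients who replied, not all those recruited in randomised practices.

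That is harmless only if reply is unrelated to adherence given the variables in the model. There is reason to doubt this. The scale asks patients to report that they did not follow a plan they had agreed with their GP. The intervention also works on communication and involvement, so it could change who replies as well as who adheres. If reply depends on adherence, the reported adherence levels and risk difference are distorted. If the dependence differs between arms, the comparison itself is distorted.

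**Working it through.** **The plan's own figure.** Sample size puts 95% of GP-level non-adherence between 0.08 and 0.50 (control) and between 0.04 and 0.25 (intervention). On the log scale the SD is ln(0.50/0.08)/(2 × 1.96) = 0.4675, and ln(0.25/0.04) gives the same value. Simulating 40 practices of 7 patients per arm, two-sided 5%, gives power of 87-88% if 20% and 10% are the medians of the GP distribution and about 84% if they are the means. One-sided and logit-scale variants bracket the stated 90%, and 7 per GP is a minimum, so the 90% is not challenged here. The 280 patients per arm equal 40 × 7, so that minimum has no margin for excluded replies.

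**Formula.** Let q be true non-adherence, a the reply rate of adherers and b that of non-adherers.

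- Observed non-adherence = qb / (qb + (1 − q)a).
- Observed odds = true odds × b/a. If b/a is the same in both arms it cancels from the odds ratio.

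The values of q come from Sample size. All values of a and b are assumptions.

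**Same reply pattern in both arms, a = 90%, true 20% v 10%**

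| b | Control | Intervention | Difference | Odds ratio | Power |
|---|---|---|---|---|---|
| 70% | 0.14/0.86 = 16.3% | 0.07/0.88 = 8.0% | 8.3 points | 2.25 | 73-78% |
| 60% | 0.12/0.84 = 14.3% | 0.06/0.87 = 6.9% | 7.4 points | 2.25 | 67-73% |
| 50% | 0.10/0.82 = 12.2% | 0.05/0.86 = 5.8% | 6.4 points | 2.25 | 61-66% |

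The true odds ratio is (0.20/0.80)/(0.10/0.90) = 2.25. The risk ratio rises slightly: 14.3/6.9 = 2.07 against a true 2.00. Power is from a cluster-level test of the difference in proportions; each range spans the mean and median readings above.

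**Benchmark: replies missing completely at random.** There is no bias, and power is 81-85% at 90% response and 77-82% at 80%. Part of the power loss in the table is therefore simply fewer replies.

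**Reply pattern differs by arm, no true effect (20% in both), a = 90%**

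- Non-adherers reply 70% in control, 50% in intervention: 16.3% v 12.2%, a spurious 4.1 points in favour of the intervention. The observed odds ratio is 0.70/0.50 = 1.40 and the rejection rate about 20% instead of 5%.
- 80% v 50%: 0.16/0.88 = 18.2% v 12.2%, a spurious 6.0 points. The odds ratio is 0.80/0.50 = 1.60 and the rejection rate about 36%.
- 50% in control, 70% in intervention: the same 4.1 points against the intervention, rejection again about 20%.

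**Counting non-responders as non-adherent.** The apparent rate becomes 1 − (1 − q)a. With q = 20% and a = 90% in both arms it is 1 − 0.80 × 0.90 = 28% in each, so the spurious difference disappears. But if adherers reply at 80% in control and 90% in intervention it gives 36% v 28%, a new spurious 8 points. It is useful as a sensitivity analysis, not as the primary method.

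**The case against.** The strongest reply is that nothing here is shown to be biased. The article contains no response rate, no reason for non-response and no link between stopping treatment and not replying. The Background figure that 50% of patients stop this medication within 6 months says nothing about who returns a questionnaire. This stands: the bias is a risk that depends on assumed reply rates.

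A reader might infer that the rule flatly contradicts intention to treat. It does not. Responders are still analysed in their practice's randomised group, so allocation is respected; what is lost is completeness.

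A reader might also take the rule to delete cases for every outcome. The sentence speaks of responses and directly follows the one on questionnaire data. Prescriptions and health-service contacts come from a register and need no reply. It could even be read as covering missing items only, or as keeping a patient's 3-month reply when the 6-month one is absent. Under any of these readings, a patient who returns no follow-up questionnaire has no self-reported adherence to analyse.

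Nor does exclusion necessarily shrink a true effect. With equal reply patterns the odds ratio is unchanged and the risk ratio rises slightly; only the risk difference shrinks. Because a binomial regression is planned and its link is not named, the serious threat is a pattern that differs by arm, and its direction cannot be predicted.

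Finally, imputation detail and sensitivity analyses are commonly left to an analysis plan, and their absence here is no fault. The point rests on the rule that the article does state.

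**Conclusion.** The concern holds in limited form. The protocol fixes an exclusion rule that takes non-responders out of the primary self-reported analysis, fits poorly with an unqualified intention-to-treat promise, and carries an assumption that is nowhere stated.

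Under the assumed patterns shared by both arms, the 10-point difference is seen as 6.4-8.3 points with the odds ratio intact. Under the assumed patterns that differ by arm, a spurious 4-6 points and a rejection rate of 20-36% can arise under the null, for or against the intervention. If replies are missing completely at random there is no bias, only lost precision.

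The documents do not support saying that the result will be biased, that patients who stop treatment are the least likely to reply, or that the bias would favour the intervention. The rule is still worth replacing before analysis, because the data for a better method are already being collected.

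**What to change.** For the questionnaire outcomes, replace the exclusion sentence with the following:

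- **Population.** All recruited patients, analysed in their practice's randomised group.
- **Primary handling.** A stated missing-at-random assumption, with multilevel multiple imputation by arm (practice as the cluster level) and 3-month responses, baseline data and register prescriptions as predictors.
- **Sensitivity analyses.** (1) Non-responders counted as non-adherent. (2) Delta shifts in the imputed log-odds of non-adherence, allowed to differ by arm. The assumed patterns above imply odds of non-adherence in non-responders (0.3/0.1)/(0.7/0.9) = 3.9 to (0.5/0.1)/(0.5/0.9) = 9 times those in responders, so shifts from 0 to about ln 9 = 2.2 would cover them.

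Use register prescriptions as an auxiliary variable or a check, not as a substitute for the primary outcome. The outcome is adherence to the chosen treatment, and the Background counts no treatment among the possible choices, so a prescription record cannot classify every patient.

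The cost is new wording and modest extra analysis work, with no new data. Imputation under missing at random removes bias only as far as the predictors explain non-response, which is why the sensitivity analyses are needed, and it will not restore all the precision lost to missing replies.

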## Discussion

Preventive treatment is fraught with uncertainty about the "true state" of health of asymptomatic patients at risk of becoming seriously ill. Both GPs and patients find it complicated to talk about the risk numbers and risk formats that may be a substantial part of the deliberation. This study aims at providing GPs and patients with a firm basis for active deliberation about preventive treatment options, with a view to optimising adherence to chosen treatment. The study results will provide a basis for recommendations about ways to communicate risk and facilitate shared decision-making during general practice consultations. The interviews and observations will allow the researchers in the project group to describe and support the learning processes during the training sessions in the complex intervention. This gives the opportunity to make the content, processes, methods and challenges as transparent as possible in the reporting of the results, adding much needed experience gathering about the possible 'active ingredients' of complex interventions in risk communication and shared decision-making. This will be interpreted to inform future implementation strategies for similar interventions in primary care.

## Ethical aspects

The study will be conducted according to the Helsinki Declaration. It has been notified to the Danish Data Protection Agency and collection of data will be handled according to their guidelines. The study is exempted from obligation of notification for the Scientific-ethical committee (pursuant to § 8 [3] of the rules of the committee) but follows the ethical code of American Anthropological Association [70]. It has been registered at ClinicalTrials.gov: NCT01187056.
